## **5. Study population**

### **5.1. Screening data**

The total number of patients initiating biological therapy screened for eligibility was not registered. An estimate will be calculated based on the usual number of patients initiating biological therapy per month at each clinical center multiplied with the number of months the center has participated in patient enrolment.

### **5.2. Eligibility**

#### **5.2.1. Inclusion criteria**

- Patients with a verified diagnosis of CD, UC, RA, axSpA, PsA, PsO, HS or niU
- Initiation of biological therapy

#### **5.2.2. Exclusion criteria**

- Age <18 years
- Unable to read and understand Danish
- Mentally unable to answer the questionnaire

### **5.2. Recruitment**

A flow chart adapted from <http://www.consort-statement.org/> will be used to visualize the flow of participants; showing the number of people screened, reasons for ineligibility, the number of participants who consented and the number analyzed (summarized by type of exposure, i.e., dietary profile) (fig. 1).

### 5.3. Adherence and reasons for withdrawal

The number of patients adhering to the protocol, i.e., those who continued the biological treatment from baseline to the follow-up visit, will be accounted for in the flowchart. Likewise, the flowchart will also account for the number of patients deviating from the protocol, i.e., they did not initiate biologic treatment after all, they ended treatment due to either adverse events or lack of efficacy, or they withdrew their consent (fig. 1).

### 5.4. Baseline patient characteristics

Baseline characteristics will be summarized by dietary profile and are displayed in table 1 (manuscript outline). The information is extracted from the baseline clinical assessment together with the baseline questionnaire which was sent electronically to the participants prior to treatment initiation. Data will be presented as means with standard deviations (SD) when normally distributed or as median with interquartile range in case of skewed data. Dichotomous and categorical variables will be presented in proportions.

The table will include information on age, sex, anthropometrics (height, weight and BMI), smoking status, diagnosis, disease duration, medication (current medication and number of previous biological medications used), patient reported outcome measures (short health scale, SF-12 physical component summary [PCS], SF-12 mental component summary [MCS]), nutrition (intake of energy, fiber and red and processed meat) as well as physician global assessment and CRP.

## 6. Analysis

### 6.1. Outcome definitions, measurement and calculation

#### 6.1.1. Primary outcomes

The primary endpoint [2] is the proportion of patients with a clinical response to therapy 14-16 weeks after initiation of treatment with a biological agent. Thus, the primary outcome will be a composite depending on the disease specific definitions of clinical response, defined below:

- CD/Crohn's disease: clinical remission, defined as Harvey-Bradshaw Index (HBI) of 4 or less [25].
- UC/Ulcerative colitis: clinical remission, defined as Mayo Clinic Score of 2 or less (with no individual subscore of >1) [26-28].
- RA/Rheumatoid arthritis: clinical response, defined as at least a 20% improvement according to the criteria of the American College of Rheumatology (ACR20) [29, 30].
- AxSpA/Axial spondyloarthritis: clinical response, defined as at least a 20% improvement according to the Assessment of Spondyloarthritis International Society (ASAS20) [31, 32].
- PsA/Psoriatic arthritis: clinical response, defined as at least a 20% improvement according to the criteria of ACR20 [33].
- PsO/Psoriasis: clinical response, defined as at least a 75% improvement in the Psoriasis Area and Severity Index (PASI 75) [34].

For the measurement and calculation of HBI, Mayo Clinic Score and PASI see table A. ACR20 and ASAS20 are composite outcome measures defined below with composites further explained in table A.

ACR20 is a composite measure developed by the American College of Rheumatology for assessment of improvement of RA patients in clinical trials [30] but also used for assessment of PsA [33]. ACR20 is defined as  $\geq 20\%$  improvement in tender and swollen joint counts and  $\geq 20\%$  improvement in at least three out of the following five measures: 1) pain, 2) patient global assessment, 3) physician global assessment, 4) self-assessed

physical disability and 5) CRP or erythrocyte sedimentation rate. Information for calculation of ACR20 will be extracted from the Simplified Disease Activity Index (SDAI; patients and physicians global assessment and tender and swollen joint count) and the Health Assessment Questionnaire Disability Index (HAQ-DI; disability, see table A), while pain is a separate question in the self-administered questionnaire ("how much pain due to your arthritis do you suffer from, the past two days?") on a VAS 0-100 mm.

The ASAS20 improvement criteria are developed by the Assessment of SpondyloArthritis international Society and includes four domains [32]: 1) Patient Global Assessment, 2) Pain, 3) Function and 4) Inflammation. In order to meet the ASAS20 response, at least three of the four domains should improve by  $\geq 20\%$  and an absolute improvement of  $\geq 10$  units (on a 0-100 scale). In the remaining domain, there should be no worsening of  $\geq 20\%$  and  $\geq 10$  units (on a 0-100 scale). Information for calculation of ASAS20 is extracted from the Bath Ankylosing Spondylitis Disease Activity Index (BASDAI; pain and inflammation) and the Bath Ankylosing Spondylitis Functional Index (BASFI; function, see table A). Patient Global Assessment is extracted from a separate question in the self-administered questionnaire ("how much does your arthritis as a whole affect your life at present?") on a VAS 0-100 mm.

### 6.1.2. Key secondary outcome measures

Predefined key secondary outcomes include changes in generic outcomes from baseline to follow-up (14-16 weeks after treatment initiation) consisting of both clinical and patient reported outcomes (PRO):

- Health-related quality of life (HRQoL): the physical component summary from the Short Form Health Survey (SF-12 PCS)
- HRQoL: the mental component summary measure from the SF-12 (SF-12 MCS)
- HRQoL: symptom burden (from the short health scale [SHS])
- HRQoL (Disability): functional status (SHS)
- HRQoL: disease-related burden (SHS)
- HRQoL: general well-being (SHS)
- Acute phase reactant (CRP)
- Physician global assessment (0-100 mm VAS)
- Patient global assessment (0-100 mm VAS)

In addition, however not specifically defined in the published protocol:

- The proportion of patients continuing the biologic treatment (yes/no) at week 14-16.

The 12-item SF-12 is a shorter form of the Short Form 36 (SF-36) which is widely used for measuring HRQoL and has a range of 0-100 (higher values indicate better health), mean of 50 and a standard deviation of 10. The SF-12 questionnaire comprises questions about physical and social functioning over the past 4 weeks. From the SF-12, two summary measures can be estimated; PCS and MCS [35].

The Short Health Scale (SHS) is a four-item questionnaire assessing the patient's subjective experience of how their disease influences four health dimensions: 1) symptom burden (severity of symptoms, 0 = none, 100 = worst thinkable), 2) functional status (impact on daily activities, 0 = none, 100 = severely impaired function), 3) disease-related burden (concern over illness, 0 = none, 100 = constantly) and 4) general well-being (0 = good, 100 = terrible) [36]. The four questions are graded from 0-100 and presented individually, where higher

scores indicate negative experience. The SHS has been validated as a measure for HRQoL for use in UC [36] and CD [37].

CRP: Blood samples as specified in the protocol were collected by a trained laboratory technician and handled according to set procedures. Results from analysis of blood samples will be limited to CRP (mg/L) in this study.

Physician global assessment and patient global assessment\* is assessed on 100 mm VAS.

\* Patient global assessment is not collected for PsO, CD and UC.

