### 3.2. Sample size and power considerations

Deciding on sample size is a well-known difficulty with exploratory prognostic factor research studies. To obtain an adequate number of outcome events, we applied 'the rule of thumb', whereby 10 outcomes are needed for

each independent variable. We planned to enroll 320 patients in total with the anticipation that 50% of these would experience a clinical response within the 14–16 weeks period after initiation of biological therapy. With this in mind and anticipating that we would observe at least 160 events (i.e., clinical response among the 320 patients), the study would be sufficiently powered to explore the impact of as many as 16 independent variables including condition and clinical center. Since using the ‘rule of thumb’ method to justify sample size is a debated practice, we went one step further and estimated the statistical power to detect differences between two dietary groups. For the contrast between groups and for a comparison of two independent binomial proportions (those with high-fiber, low-meat intake vs. other) using Pearson’s  $\chi^2$  statistic, with a  $\chi^2$  approximation, with a two-sided significance level of 0.05 ( $P < 0.05$ ), a total sample size of 318—assuming an ‘allocation ratio’ of 1 to 2 (one-third)—has an approximate power of 0.924 (i.e., >90% statistical power) if the anticipated proportions responding to therapy are 60% and 40%, respectively. However, due to pre-specified time constraints, inclusion to BELIEVE was terminated on 03-30-2020 before reaching the planned sample size of 320 patients in total.

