**Clinical examination**

Physician global assessment (0-100 mm VAS), median (IQR)  
CRP, mean (SD), mg/L

\*Will be estimated by comparing groups using the standardized mean difference (SMD); an SMD above 0.5 SD-units will be evaluated as a potential (data driven) confounding variable. HFLM; High fiber/low meat (exposed), LFHM; low fiber/High meat, CID; Chronic Inflammatory Disease, NSAID; Non-steroidal Anti-Inflammatory Drugs, PROs; patient reported outcomes, HRQoL; Health related quality of life, SF-12; 12-item Short Form survey, PCS; physical component summary, MCS; mental component summary, VAS; visual analog scale, CRP; C-reactive protein

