|------------------------------------------------------------------------------------------------------------------------------------------------------------------------------------------------------------------------------------------------------------------------------------------------------------------------------------------------------------------------------------------------------------------------------------------------------------------------------------------------------------------------------------------------------------------------------------------------------------------------------------------------------------------------------------------------------------------------------------------------------------------------------------------------------------------|------|------|---------------------|-----------------------------|---------------------|----------------------------------------|---------------------|
| Outcome                                                                                                                                                                                                                                                                                                                                                                                                                                                                                                                                                                                                                                                                                                                                                                                                          | HFLM | LFHM | Difference (95% CI) | P value*                    | Difference (95% CI) | P value*                               | Difference (95% CI) |

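### The key secondary outcome CRP is set up as a raw change in mg/L, with no transformation, robust method or baseline-CRP covariate; if CRP is right-skewed, a few high values dominate it and power is low

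*SAP*

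**What the plan says.** Section 6.1.2 lists CRP among the key secondary outcomes, all but one of which are changes from baseline to week 14-16. On measurement it says "Results from analysis of blood samples will be limited to CRP (mg/L) in this study". That sentence settles which laboratory result is reported and its unit, not how it is analysed.

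The scale has to be read from the table shells. Table 2 has a row for ΔCRP in mg/L under the column head "Difference (95% CI", with a P value. The same row appears in Appendix Tables 2, 3 and 4.

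Section 6.2 says only that the key secondary outcomes get analyses similar to the logistic models of the primary outcome. The Table 2 footnotes list CID type, age, sex, clinical center and smoking, then the propensity score. Baseline CRP is not listed, and no log, rank-based or robust method is named for CRP as an outcome.

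For baseline description, section 5.4 gives means with SDs for normally distributed data "or as median with interquartile range in case of skewed data". Table 1 nevertheless pre-sets "CRP, mean (SD), mg/L", while the physician global assessment beside it is set as median (IQR).

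**The concern.** CRP cannot fall below zero and may have a long right tail; here it is pooled over six diseases. If it is skewed, the raw change in mg/L is largely driven by the few patients who start very high. The HFLM-LFHM difference then depends heavily on which diet group those patients fall in, and a moderate proportional effect on CRP would usually be missed.

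CRP is the only laboratory measure among the ten key secondary outcomes. A null result on the raw scale would be hard to interpret, and a move to logs after seeing the data would be post hoc.

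The same tail affects Table 1. Its footnote uses a standardized mean difference above 0.5 to flag data-driven confounders. A raw SD inflated by a few values makes that flag insensitive for CRP.

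**Working it through.** **1. The SAP's own power figure.** Section 3.2 works "with a two-sided significance level of 0.05" and states that the design "has an approximate power of 0.924" "if the anticipated proportions responding to therapy are 60% and 40%, respectively". With 318 patients split 1:2, the groups are 106 and 212.
- Pooled proportion: (106 × 0.60 + 212 × 0.40)/318 = 0.4667.
- SE under the null: √[0.4667 × 0.5333 × (1/106 + 1/212)] = 0.05935.
- SE under the alternative: √[0.24 × (1/106 + 1/212)] = 0.05828.
- Power: Φ[(0.20 − 1.96 × 0.05935)/0.05828] = Φ(1.436) = 0.9245.

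The stated figure reproduces. It concerns only the binary primary outcome; the SAP has no SD, effect size or power for CRP.

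**2. Assumptions for CRP (none from the SAP).** Log-normal CRP; medians 8 mg/L at baseline and 3.6 mg/L at follow-up; SD of ln CRP 1.0-1.5; correlation of ln values 0.3-0.5; groups 106 and 212; follow-up CRP lower in HFLM by a ratio of 0.6 or 0.7; two-sided 5% test. The coefficient of variation is √(exp(SD²) − 1), which is 1.31 at SD 1.0 and 2.91 at SD 1.5, so the raw SD exceeds the mean throughout.

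**3. Middle case by formula (SD 1.25, correlation 0.5, ratio 0.6).**
- Means are median × exp(1.25²/2) = median × 2.184: baseline 17.47, follow-up 7.86 (LFHM) and 4.72 (HFLM). The difference in mean change is 3.14 mg/L.
- SD of raw change, from the log-normal variances and covariance: about 32.5 (LFHM) and 32.2 (HFLM). SE ≈ √(32.2²/106 + 32.5²/212) ≈ 3.84; z ≈ 0.82; power ≈ 13%.
- Log follow-up adjusted for log baseline: residual SD 1.25 × √(1 − 0.25) = 1.083; SE 1.083 × √(1/106 + 1/212) = 0.129; z = 0.511/0.129 = 3.97; power ≈ 98%.

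**4. Simulated power.**

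| Analysis | Middle case | Whole range |
|---|---|---|
| Raw change, no baseline CRP | 16% | 7-27% |
| Change in ln(CRP+1), no baseline CRP | 85% | 31-97% |
| Raw change, baseline CRP as covariate | 68% | 18-96% |
| ln follow-up, ln baseline as covariate | 97% | 52-100% |

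The formulas in step 3 agree with the first and last rows to within a few points.

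**5. A second set of assumptions.** Here the median was 6 mg/L, SD of ln CRP 0.6-1.4, correlation 0.3-0.7, CRP halved overall, and the diet effect was sized so that the baseline-adjusted log analysis has about 80% power. Raw change had 10-22%, log change 59-74%, and raw change with baseline CRP 30-73%. The 5% of patients with the most extreme changes carried 47-85% of the sum of squares. With CID type in the model and overall follow-up/baseline ratios of 0.3 to 1.0, raw change had 8-41%; the 41% needs mild skew (SD 0.8) and no overall fall in CRP. A total of 200 patients, assumed because recruitment stopped short of 320, gave the same pattern. Under no effect the raw test rejected in 5.3% of runs.

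**The case against.** **The shells do not strictly fix a mean difference.** Table 2 belongs to a manuscript outline, and its column head also sits over clinical response, which section 6.2 reports as an odds ratio. This stands in part: no model for continuous outcomes is named. But the row label fixes change in mg/L, and nothing elsewhere offers another scale.

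**Much of the power gap is baseline adjustment, not scale.** This stands. In the middle case, staying in mg/L and adding baseline CRP lifts power from 16% to 68%. A reader might infer that skewness alone costs most of the power; the figures do not support that. Scale still matters after adjustment (68% against 97%), and more so at SD 1.5.

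**The inputs are assumed, and a proportional effect favours logs.** This stands as a limit on the size. In further runs with a constant mg/L shift, raw change had 73-79% power and the log analyses about 100%. That shift also raises the floor of one group, so it is an artificial case.

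Four other inferences are tempting but not supported:
- *The plan itself logs CRP.* The logarithm in Table A belongs to the DAS28-CRP formula; SDAI, also in Table A, adds CRP untransformed.
- *Imputation will produce negative CRP.* That needs a normal imputation model, and section 6.3 states none for CRP.
- *A failed CRP test drags down the whole Hochberg list.* If only CRP fails, the next threshold is 0.05/2; going lower requires other outcomes to fail too.
- *The test is invalid.* Its type I error stays near 5%.

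**Conclusion.** The point holds as a weakness in precision and pre-specification for one of ten key secondary outcomes. The SAP sets CRP up as a raw change in mg/L without transformation, robust method or baseline-CRP covariate, and its Table 1 entry does not follow the section 5.4 rule if CRP is skewed.

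Under the step 2 assumptions, the raw change has about 7-27% power where a baseline-adjusted log analysis has 52-100%. Both scale and missing baseline adjustment contribute. The direction is consistent over the ranges tried, but the size cannot be derived from the SAP and shrinks with milder skew. The primary analysis is untouched.

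**What to change.** - **Sections 6.1.2 and 6.2, Table 2 and Appendix Tables 2-4:** analyse ln(CRP) at follow-up by linear regression, adjusted for ln(baseline CRP) and the covariates already listed. State a rule for values below the assay limit.
- **Reporting:** give the ratio of geometric means with 95% CI, and medians (IQR) in mg/L alongside. If ln(CRP+1) is preferred, label the result a ratio of CRP+1. At the medians a true ratio of 0.60 becomes (0.60 × 3.6 + 1)/(3.6 + 1) = 0.69; averaged over the assumed distribution it is about 0.70.
- **Imputation:** if CRP is imputed, do it on the log scale.
- **Table 1:** show CRP as median (IQR) and compute its standardized mean difference on the log scale.

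The cost is SAP wording and one transformation in the code. The downside is that the effect becomes a ratio rather than a difference in mg/L, which is why the medians should stand beside it.

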## 2.5. Objective

To examine if treatment outcomes in patients with CID vary with dietary differences.

Primary objective: To compare the differences in clinical response following high intake of fiber *AND* low intake of red/processed meat, relative to a low intake of fiber *AND* high intake of red/processed meat, on the proportion of individuals achieving a clinical response (defined individually according to their specific condition) after a period of 14-16 weeks, in patients with CID.

Key secondary objectives: To compare the differences in clinical response following high intake of fiber *AND* low intake of red/processed meat, relative to a low intake of fiber *AND* high intake of red/processed meat, on changes in measures of health-related quality of life and disability (SF-12 physical component summary [PCS] and mental component summary [MCS], and the short health scale components), C-reactive protein (CRP), physician global assessment, and patient global assessment from baseline to week 14-16, as well as the proportion of individuals continuing biologic therapy at week 14-16, in patients with CID.

Exploratory secondary objectives: (i) To compare the effect of high intake of fiber relative to a low intake of fiber while adjusting for meat intake, on the proportion of individuals achieving a clinical response (defined individually according to their specific condition) after a period of 14-16 weeks, in patients with CID; (ii) To compare the effect of low intake of red/processed meat, relative to a high intake of red/processed meat while adjusting for fiber intake, on the proportion of individuals achieving a clinical response (defined individually according to their specific condition) after a period of 14-16 weeks, in patients with CID.

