## 3. Study methods

### 3.1. Study design

BELIEVE is an observational multi-center cohort study with prospective enrollment of CD, UC, RA, axSpA, PsA and PsO patients initiating treatment with a biologic agent (or switching to another). Treatment with biologics was assigned to the patients independent of BELIEVE and their habitual diet. When a patient was found to be a candidate for initiation of biologic treatment or switching to another biologic agent, they were invited to participate in the study. Patients were examined at two time points; at baseline and 14-16 weeks after treatment initiation, according to Danish clinical standards. The examination program included questionnaires (including a Food Frequency Questionnaire at baseline), clinical assessment and sampling of blood, urine, feces and intestinal biopsies (the latter only for UC and CD). The inclusion period was between 1st of September 2017 and 31st of March 2020 with follow-up until end of July 2020. The following centers in Denmark participated in inclusion of patients to BELIEVE: Department of Hepatology and Gastroenterology, Aarhus University Hospital; Diagnostic Centre, Silkeborg Regional Hospital; Department of Gastroenterology, Herlev and Gentofte Hospital; Medical Department, Hospital Sønderjylland; Department of Gastroenterology, Hospital of South West Jutland; Department of Medical Gastroenterology, Department of Rheumatology and Department of Dermatology and Allergy Centre, Odense University Hospital.

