## **4. Statistical principles**

### **4.1. Statistical significance and confidence intervals**

All P values and 95% confidence intervals will be two sided. We will not apply explicit adjustments for multiplicity, rather we will interpret the analysis of the key secondary outcomes according to the Hochberg sequential procedure [21]: The analyses of the key secondary outcomes will be performed, and the correspondent P values will be ordered from largest to smallest in a list. If the largest P value is less than the significance level of 0.05, then all the tests are considered significant. In contrast, if the largest P value fails to show statistical significance, then progressively more stringent P values are applied as a significance level (the second largest P values: 0.05/2, the third largest: 0.05/3 and so on). When a test succeeds to show a statistically significant difference, then the remaining tests downstream from this are considered significant. Thus, comparisons continue until a test shows a statistical difference or until all comparisons are made. The key secondary statistical tests will be reported with P values for hypothesis tests and claims of potential statistical significance. Further, due to potential issues of multiplicity as multiple tests will be performed, we will interpret ‘statistically significant’ findings in the context of whether the 95% confidence interval (CI) excludes outcomes that could be perceived as clinically important.

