### 6.3. Missing data

As previously stated (under section 4.3), the primary analyses will be based on the ITT population. Accordingly, participants will be followed up, assessed and analyzed as members of their initial dietary group, irrespective of their adherence to the planned course of treatment with biological agents and potential personal changes in dietary habits (i.e., independent of withdrawals and cross-over phenomena). Every effort will be made to minimize missing data (i.e. both baseline covariates [ $X$ 's] and outcome data [ $Y$ 's]). Loss to follow-up and missing data for various reasons is however difficult to avoid in pragmatic, real-world observational studies, from clinical practice.

We will apply the analysis framework suggested by White et al (2011) in which missing data related to the ITT approach depend on making plausible assumptions about the missingness of the data and including all participants in subsequent sensitivity analyses [24]:

**#1. Attempt to follow up all participants who signed informed consent**, even if they withdrew from allocated treatment or significantly modified their dietary habits (i.e., we contact all individuals unless they explicitly stated that they had withdrawn their consent).

**#2. Perform a main analysis of all observed data that are valid under a plausible assumption.** For our primary analyses we will assume that data is 'Missing At Random' (MAR). The MAR assumption requires that, conditional on the observed data for the case,  $Y_{obs}$ , the probability that a value is missing does not depend on the true values of the missing items,  $Y_{mis}$ . Multiple imputation (MI) will be used to account for participants from whom we have an answered FFQ (i.e. the ITT population) but potentially with missing outcome information at follow-up.

**#3. Perform sensitivity analyses.** In order to explore the effect of departures from the assumption made in the main analysis (#2) other analysis techniques will be applied; these models will potentially be informative even if data are 'Missing Not At Random' [MNAR].

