| ΔPatient global assessment (0-100 mm VAS)                                                                                                                                                                                                                                                                                                                                                                                                                                                                                                                                                                                                                                                                                                                                                                        |      |      |                     | n.a.                        |                     | n.a.                                   | n.a.                |
| Continuation of treatment, n (%)                                                                                                                                                                                                                                                                                                                                                                                                                                                                                                                                                                                                                                                                                                                                                                                 |      |      |                     |                             |                     |                                        |                     |

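### Patient global assessment is a cohort-wide key secondary outcome but is not collected in three of the six diseases, and its place in the Hochberg family is contradictory

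*SAP*

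**What the plan says.** Section 3.1 describes "prospective enrollment of CD, UC, RA, axSpA, PsA and PsO patients", so six diseases make up the cohort. Section 2.5 includes "physician global assessment, and patient global assessment from baseline to week 14-16" in the key secondary objective, which is set for patients with CID without restriction by disease. Section 6.1.2 opens its list with "Predefined key secondary outcomes include changes in generic outcomes from baseline to follow-up" and includes patient global assessment there. The list has nine change outcomes plus continuation of biologic treatment, ten in all. A note at the end of the same section then states: "Patient global assessment is not collected for PsO, CD and UC".

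Four other parts of the SAP bear on how this outcome would be handled:

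- Section 4.3 defines the intention-to-treat population as all consenting participants who answered the FFQ, whatever their disease.
- Section 6.2 extends the primary outcome's analyses to the key secondary outcomes.
- Section 6.3 says "Multiple imputation (MI) will be used to account for participants from whom we have an answered FFQ" but who may have no outcome at follow-up. It makes no exception for an item that is not collected in a given disease.
- Section 4.1 puts the P values of the key secondary outcomes into one Hochberg list and adds "The key secondary statistical tests will be reported with P values for hypothesis tests". It does not state the number of tests.

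In Table 2 the row that begins "ΔPatient global assessment (0-100 mm VAS" has n.a. in its P value cells, and Appendix Tables 2, 3 and 4 do the same. It is the only key secondary row so marked. The other rows with that mark are the disease-specific sub-components of the primary outcome and the harms.

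**The concern.** Two things are unsettled. The first is the population. The objective asks for an effect across all CIDs, but the data can exist only in RA, axSpA and PsA. An analyst has to choose between analysing those three diseases and filling in the other three, and the SAP does not say which. A figure presented for the whole cohort would be an arthritis result under a wider label.

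The second is multiplicity. The text implies a family of ten and the table shells imply nine. In a Hochberg procedure the number of tests, and any large P value among them, affects whether outcomes with smaller P values are declared significant. If membership is left open until results are available, that choice can be made with the P values in view.

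**Working it through.** **Plan's own figure.** The SAP gives no sample-size or power figure for patient global assessment. Its only power figure is for the primary outcome (section 3.2: N = 318, split 106 to 212, 60% against 40%, two-sided 0.05). Pooled proportion = (106×0.6 + 212×0.4)/318 = 0.4667. Standard error under the null = √[0.4667×0.5333×(1/106 + 1/212)] = 0.0593; under the alternative = √[0.24/106 + 0.24/212] = 0.0583. Power = Φ[(0.20 − 1.96×0.0593)/0.0583] = Φ(1.436) = 0.9245, which agrees with the stated 0.924. This figure does not depend on the present point.

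**Share of patients without the item.** Inputs are the planned quotas in section 4.2: 100 IBD, 100 RA and 120 in the remaining diseases, 320 in total. The number with psoriasis is not given, so a range is shown.

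| Assumption on the group of 120 | Without the item | Share of 320 | With the item |
|---|---|---|---|
| No psoriasis | 100 | 31% | 220 |
| Equal thirds axSpA, PsA, PsO | 140 | 44% | 180 |
| None with axSpA or PsA | 220 | 69% | 100 |

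**Precision where the item exists.** With a 1:2 split, 80% power and two-sided 0.05, the detectable standardised difference is (1.960 + 0.842)×√(3/N + 3/(2N)). This gives 0.33 at N = 320, 0.40 at 220, 0.44 at 180 and 0.59 at 100.

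**What imputation could add.** No value is observed in CD, UC or PsO at either visit, so neither the level nor the diet effect in those diseases can be estimated. A simulation shows the consequence. It assumed N = 320, an effect of −10 mm where the item is collected and 0 elsewhere, SD 25 mm, five imputations (the SAP's setting) and 1,000 replications.

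| Share missing | Imputed, all patients | Collected diseases only | True all-CID average, −10×(1 − share) |
|---|---|---|---|
| 31% | −10.1 | −10.2 | −6.9 |
| 44% | −10.2 | −10.2 | −5.6 |
| 69% | −9.8 | −9.7 | −3.1 |

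The imputed estimate is the arthritis estimate. Its distance from the true average follows from the assumed zero effect and would vanish if the effect were equal in all diseases. The data cannot distinguish these cases.

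**Family size.** Hochberg compares the i-th largest P value with 0.05/i. The last threshold is 0.05/9 = 0.0056 with nine tests and 0.05/10 = 0.0050 with ten. Two constructed examples:

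- Smallest P value 0.0054 and eight at 0.3. With nine tests, 0.0054 < 0.0056 and one outcome is significant. Add patient global assessment at P = 0.4, and 0.0054 > 0.0050, so none is.
- Nine P values of 0.04. With nine tests, 0.04 < 0.05 and all nine are significant. Add patient global assessment at P = 0.2: 0.2 fails against 0.05, 0.04 fails against 0.025 and every stricter threshold, and none is significant.

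An added P value moves only the outcomes that rank below it, meaning those with smaller P values, and each of these then faces a stricter threshold.

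**The case against.** The note in section 6.1.2 discloses the gap, and the n.a. cells are consistent across four tables, so the authors probably meant to show this outcome without a test. On that reading the promise of P values in section 4.1, which concerns tests, is not broken. Much of this stands, and it is the reason for adopting the tables' reading in the fix. It does not remove the conflict with the ranking of key secondary outcomes in section 4.1 or with the unrestricted objective in section 2.5.

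A reader might infer that the SAP plans to fabricate values for CD, UC and PsO. It does not say so. Section 6.3 speaks of the primary analyses and of outcomes missing at follow-up, its imputation steps are written for logistic regression of clinical response, and patient global assessment is not named. Imputation reaches it only by reading sections 4.3, 6.2 and 6.3 together. Appendix Table 2 gives that reading some support, since it lists complete-case analysis of this row as a sensitivity analysis. The defect is the missing exception.

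A reader might also infer that family size alters the threshold for all nine other outcomes. It alters only those with smaller P values, and the reversals above use P values chosen to show that they can occur. Section 4.1 presents the procedure as a guide to interpretation.

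Finally, it is tempting to say that the item differs between diseases. Section 6.1.1 gives the axSpA question ("how much does your arthritis as a whole affect your life at present"), but the SAP gives no question wording for RA or PsA, so a difference cannot be shown.

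**Conclusion.** The point holds. As the SAP stands, a cohort-wide effect on patient global assessment is an objective that the data cannot meet, because three of six diseases do not supply the item. The affected share is 31% to 69% at the planned quotas. The range rests on assumptions about the number with psoriasis, and enrolment closed short of 320, so the actual share is unknown. The missing-data rule has no exception for this by-design absence, and imputation would only relabel the arthritis estimate; it would not distort that estimate within arthritis. The Hochberg family is ten by the text and nine by the tables, which can change conclusions for outcomes with smaller P values.

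The primary outcome is not at risk: patient global assessment enters it only through ACR20 and ASAS20, which are used in the diseases where the item is collected.

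**What to change.** - **Sections 2.5, 6.1.2 and 6.2:** restrict the analysis of patient global assessment to RA, axSpA and PsA, and show n for each diet group.
- **Section 6.3:** state that an outcome not collected for a CID is not imputed for that CID.
- **Section 4.1:** state that the Hochberg family has nine tests and excludes patient global assessment, which is reported as an estimate with a 95% confidence interval. This agrees with the table shells.
- **Section 4.2:** record the change, since the outcome is listed as predefined.

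Moving the outcome to Table A is not needed and would not fit, because section 6.1.3 reserves that table for outcomes specific to one or two diseases and this one is collected in three.

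The cost is a few sentences, a deviation entry, and the loss of the outcome's cohort-wide tested status. The smaller n is not a cost of the change, since the other patients have no data to lose.
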